#### Feasibility of intensified monitoring

- The practical and logistical implementation challenges
- The time needed to set up the on-site drug level assay
- The realization of expected turnaround times
- The effect of genotyping and drug level assessment results on the choice of second line therapy

#### Cost-efficiency of intensified monitoring

Comparison of cost increases associated with the intensified monitoring strategy and cost reductions by prevention of unnecessary switches to a more costly regimen and differences in other study outcomes between arms.

#### Effect on transmission of HIV

Estimation of the effects of the intensified monitoring strategy at the population level by study of the relationships between viremia during therapy, infectivity of patients on treatment and incidence and prevalence of (drug resistant) HIV.

#### Risk factors for therapy failure

Analysis of the contribution of potential social, economical and psychological parameters to suboptimal adherence, therapy failure, and drug resistance. This will provide the opportunity for development of a scoring model for the risk of therapy failure.

#### Determinants of therapy failure

In depth studies are planned to gain insight in determinants of therapy failure.

## **Benefit, burden and risks associated with participation**

### **Immediate benefit**

Early detection of suboptimal adherence, viremia and drug resistance in patients randomised to the intervention arm, resulting in faster switching of therapeutic regimen in case of drug resistance, avoiding switching in case of no resistance, and in more effective adherence counselling in the case of non-adherence, which are all in the interest of the patient.

### **Long-term benefit**

Contribution to the development of more efficient methods of HIV-1 treatment monitoring for future patients as well as expansion in knowledge of risk factors and determinants of HIV-1 therapy failure.

### **Risks**

Blood sampling: Minimal additional risk. When blood is drawn, patients might experience slight discomfort or possible inflammation at the site where blood is drawn.

Questionnaires: Minimal risk. Participants might find certain questions of a sensitive nature. Referral to a social worker for psychosocial support will be available, if needed.

## 2 INTRODUCTION AND RATIONALE

### 2.1 Introduction

During recent years access to combination antiretroviral treatment (ART) for HIV-1 infected individuals in low- and middle-income countries (LMIC) has greatly improved. By the end of 2013, 11.7 million people in LMIC were receiving ART, of which the majority lives in sub-Saharan Africa. First-line ART regimens are provided on programmatic basis and usually consist of the Nucleos(t)ide Reverse Transcriptase Inhibitors (NRTIs) tenofovir and emtricitabine or lamivudine combined with a Non-Nucleoside Reverse Transcriptase Inhibitor (NNRTI), efavirenz (EFV). In a meta-analysis of first-line ART in LMIC we demonstrated that, despite high early mortality rates, these strategies are generally successful, with viral suppression rates of 76% after one year and 67% after 2 years of ART.

The initiation of large numbers of patients on lifelong ART commits governments to implement efficient strategies of monitoring of HIV treatment in LMIC. The development of a cost-effective approach to monitoring has been the topic of many recent studies. Several approaches to treatment monitoring have been proposed and implemented in different settings (see table 1). Early trials and modelling studies comparing viral load (VL) and CD4 monitoring with only CD4 monitoring generally concluded that implementation of viral load monitoring in LMIC would bring clinical benefit but at high cost. However, these studies generally did not take into account several important consequences of HIV therapy failure, such as ongoing viral transmission due to prolonged undetected viremia and development, accumulation and transmission of drug resistance. Moreover, these studies were performed when prices of VL measurement were substantially higher. In contrast, more recent research has stressed the benefits of implementing routine VL monitoring in LMIC, emphasizing that virological failure is an early indicator that is able to detect therapy failure before its detrimental effects occur. These insights are reflected in the 2013 WHO consolidated ART guidelines recommendation stating that, if available, VL testing should be used for monitoring of the effect of HIV treatment and detection of therapy failure. In accordance with World Health Organisation (WHO) guidelines, the South African National Department of Health (NDoH) consolidated treatment guidelines have implemented routine VL monitoring for monitoring of treatment success.

Table 1: overview of different monitoring strategies

|                              | Clinical monitoring | Immunological monitoring | Low intensity virological monitoring (2013 WHO guidelines) | High intensity virological monitoring (high-income countries) |
|------------------------------|---------------------|--------------------------|------------------------------------------------------------|---------------------------------------------------------------|
| Monitoring of symptoms       | X                   | X                        | X                                                          | X                                                             |
| Toxicity monitoring          | X                   | X                        | X                                                          | X                                                             |
| CD4 count                    |                     | 6-12 months              | 12 months                                                  | 3-6 months                                                    |
| Viral load                   |                     |                          | 12 months                                                  | 3-4 months                                                    |
| Genotypic resistance testing |                     |                          |                                                            | If elevated VL                                                |
| Drug level monitoring        |                     |                          |                                                            | (on indication)                                               |

The frequency of VL monitoring in LMIC such as South Africa is limited to yearly measurements, which is recommended by both WHO and South African NDoH guidelines. Upon detection of therapy failure as indicated by a confirmed VL >1000 copies/ml, patients are empirically switched to a second-line regimen containing a boosted protease inhibitor (PI) (ritonavir-boosted lopinavir) and two NRTI's (commonly zidovudine and lamivudine), and given intensified adherence counselling. However, in previous work we and others demonstrated that the practice of yearly VL monitoring leads to significant accumulation of drug resistance mutations and loss of options for follow-up therapeutic regimens. In the same study, it was retrospectively shown that more frequent VL measurement could considerably limit accumulation of resistance by earlier detection of therapy failure followed by switching to a second-line regimen.

Increasing the frequency of VL monitoring may prevent accumulation of resistance but may also result in higher rates of detection of therapy failure in the absence of drug resistance. In previous studies performed in low- or middle income settings of 6 monthly or yearly VL monitoring, 13-35% of patients meeting WHO criteria for therapy failure did not have drug resistance mutations warranting a switch to a second-line regimen. In high-income countries this is prevented by combining more frequent VL measurements (usually every three months in the first years of treatment) with genotypic resistance testing in case of viral rebound. If drug resistance is detected, a therapy switch to a second-line antiretroviral regimen is made. If drug resistance is not detected, this suggests that viremia is due to non-adherence, and continuation of the first-line regimen combined with intensified adherence counselling is warranted. In some cases, plasma drug levels are measured to confirm whether viremia is a result of non-adherence to therapy. As genotypic resistance testing and drug level monitoring usually require cold chain conditions for sample transport, considerable diagnostic expertise and advanced laboratory equipment, these methodologies are currently

not routinely implemented in LMIC.

Delayed detection of therapy failure may have an impact on public health. While it has been shown that levels of ART uptake decrease the risk of HIV transmission on the population level in a South African cohort, such successes may be threatened by frequent occurrence of prolonged therapy failure, which allows for increased transmission rates of (drug resistant) HIV. This is highlighted by a recent WHO survey in Africa that showed that the prevalence of transmitted drug resistance to components of first-line regimens, specifically NNRTIs, has increased after the roll-out of ART. A recent modeling study suggested that high rates of transmitted drug resistance can aggravate HIV epidemics, providing a rationale for close monitoring and prevention of transmission of drug resistance.

As stated by the WHO low-cost and easily implementable alternatives for currently available monitoring tools are urgently needed. In previous research projects we have developed two affordable tools that show the capability to be implemented in clinical treatment programs in LMIC. We and others have developed methods for on-site drug level measurement (DLM) that enables measurement of nevirapine (NVP) and efavirenz (EFV) plasma drug levels at low cost in low income settings requiring minimal laboratory infrastructure. Furthermore, we have designed a genotypic drug resistance test optimized for non-B subtypes prevalent in sub-Saharan Africa, which can be performed on dried blood spots (DBS), drastically reducing the cost of and required laboratory infrastructure for drug resistance testing. In a pilot study we have demonstrated that DBS transported at room temperature serve as a good alternative to plasma for drug resistance testing, and can be easily implemented in LMIC.

## 2.2 Rationale

ART is being rolled out to millions of patients in LMIC. While treatment programmes in LMIC are generally effective, rates of therapy failure, accumulation of drug resistance, unnecessary switching to second-line regimens and (possibly) residual transmission are relatively high. Viral load (VL) monitoring is being implemented in many countries in an effort to improve treatment programme outcomes. However, the optimal cost-efficient frequency of VL monitoring is currently unknown, and a growing body of evidence suggests that significant individual and population health gains can be achieved by expanding viral load monitoring to genotypic drug resistance testing and drug level monitoring (DLM). Conventional tools for resistance testing and DLM are generally not implemented in LMIC due to financial and infrastructural constraints. In pilot projects we have performed field studies using novel low cost solutions for resistance testing and DLM which can be implemented on the individual patient level in LMIC.

Meanwhile, price reductions of VL monitoring have added to the affordability of intensified monitoring strategies in LMIC. These recent developments result in a unique opportunity to assess the added value of intensified VL monitoring in combination with drug resistance testing, DLM, and intensified adherence counseling tailored to DLM results in LMIC.

We have developed a novel low-cost strategy for HIV treatment monitoring that enables early detection of therapy failure, drug resistance and non-adherence, while requiring minimal on-site laboratory capacity and being tailored for implementation in settings with monthly medication collection visits. The strategy consists of intensified VL monitoring every three months. In case of a viral rebound >1000 copies/ml, this will be followed up by repeat VL measurement combined with affordable on-site and real time DLM assay targeting NNRTIs. In case NNRTI concentrations are not detected in plasma tailored intensified adherence counselling is performed. In case NNRTI concentrations are detected, this will be combined with off-site DBS-based genotypic drug resistance testing. Switching to a second line regimen will only be performed if drug resistance is detected.

It is expected that intensified VL monitoring will detect therapy failure at an early stage, prior to selection of multiple resistance mutations. In those patients in which viremia is present, DLM is expected to identify patients with (nearly) undetectable plasma drug levels due to major non-adherence, in which the risk of drug resistance is expected to be lower. This will enable clinicians to provide intensified and tailored adherence counselling and prevent unnecessary resistance testing. Effective intensified adherence counselling has the potential to resuppress the VL to below 1000 copies/ml in over half of cases, if performed in an effective manner and in a setting of frequent VL monitoring.

When non-adherence is not detected by DLM, quick follow-up drug resistance testing will detect drug resistance prior to accumulation of resistance mutations and assure safe options for future treatment, preventing the use of more toxic regimens and therefore avoiding additional morbidity. It will also identify those patients in whom drug resistance mutations are absent, thus avoiding unnecessary treatment changes. Finally, as intensified monitoring is expected to reduce the duration of viremia during therapy failure it is expected to lower HIV transmission rates and transmission of drug-resistant HIV. Although the costs of intensified monitoring itself are higher, implementation of the strategy may be cost-effective or even cost saving by preventing unnecessary second-line therapy, reducing patient morbidity and mortality and reducing transmission rates.

We aim to perform a randomized controlled trial comparing the proposed novel intensified monitoring strategy with standard of care HIV-1 treatment monitoring, to be performed in adult South African HIV-1 patients who have recently initiated ART. By performing this trial we aim to investigate the benefits and cost-effectiveness of the proposed strategy of intensified monitoring relative to the standard of care. We will assess the effect of the proposed strategy on relative risk of development and accumulation of resistance, prevention of unnecessary switches to second-line therapy and viral resuppression rates. We will also study whether more intensified monitoring has an impact on patient health. Using mathematical modeling, the effect of different monitoring strategy on the transmission of (drug resistant) HIV will be estimated. We aim to collect additional data on sociological, economic, psychological and behavioral risk factors for non-adherence and therapy failure. Investigation of the proposed strategy in a controlled fashion will also allow for future in depth study of immunological, virological and pharmacological mechanisms underlying therapy failure.

## 3 OBJECTIVES

### 3.1 Primary objective – Virological effects of intensified monitoring

To assess the effect of the intensified monitoring strategy versus standard of care monitoring on (1) development and accumulation of resistance mutations and consequential loss of therapeutic options, (2) prevention of unnecessary treatment switches and (3) resuppression rates after intensified counselling.

### 3.2 Secondary objectives

#### 3.2.1 Clinical effects of intensified monitoring

To assess the impact of the intensified monitoring strategy on (1) Quality of Life (QoL), (2) patient morbidity and mortality and (3) rates of immunological recovery. Clinical effects will be studied as a secondary objective as it is unknown if the follow-up duration will allow expected differences between arms to become apparent.

#### 3.2.2 Feasibility of intensified monitoring

To assess the feasibility of the intensified monitoring strategy. The results of this study will enable assessment of the feasibility of the intensified monitoring strategy and identify practical and logistical barriers to implementation of the approach.

#### 3.2.3 Effect on transmission of HIV

To model the effects of intensified monitoring on transmission rates of (drug resistant) HIV on a population level, by using a mathematical model incorporating study results such as duration of viremia, presence of drug resistance and sexual risk behaviour as input data.

#### 3.2.4 Cost-effectiveness of intensified monitoring

To assess the cost-effectiveness and incremental cost-effectiveness ratio (ICER) of the intensified monitoring strategy, taking into account the impact on QoL, morbidity and mortality, costs related to individual patient care such as diagnostic interventions, treatment switches and hospital admissions, and cost reductions on a population level as a result of averted new infections.

#### 3.2.5 Risk factors for therapy failure

To gain insight into risk factors for therapy failure and non-adherence by correlating biological and medical parameters such as viral suppression, drug levels, drug resistance,

morbidity, mortality and QoL to a validated adherence questionnaire measuring sociological, economic and psychological parameters.

### 3.2.6 Virological, immunological and pharmacological determinants of therapy failure

To study virological, immunological and pharmacological determinants underlying therapy failure by measuring markers and comparing them between groups of failing and successfully treated patients. (Funding for this objective is not yet available, if obtained, ethics approval will be sought in an amendment to this protocol.)

## 4 STUDY DESIGN AND PATIENT POPULATION

### 4.1 Study format\*

The study format will be an open-label randomized controlled trial (RCT) in which HIV-1 infected patients initiating ART and already on ART will be enrolled. Enrolment will continue until 600 patients have been randomized. Patients initiating ART will be randomized after six months of ART and patients already on ART will be randomised at 6 months after the last viral load measurement. Patients in both arms will receive study visits every three months for a total follow-up duration of 18 months after randomisation to either of two study arms.

- Control arm: Standard of care HIV-1 treatment monitoring in accordance with South African NDOH guidelines. (see “5.1.2”)
- Intervention arm: Intensified treatment monitoring according to the treatment monitoring strategy under investigation. (see “5.1.3”)

### 4.2 Population

This study will include adult HIV-1 infected patients who are about to initiate or have already initiated first-line ART. Patient enrolment and randomisation will be performed at two different time points. Timing and criteria for enrolment and randomisation are as follows:

1. ART naïve patients: Patients are eligible for enrolment at initiation of treatment with first-line ART. Randomization is performed after availability of the first routine VL measurement, performed at month 6 of treatment.
2. Patients on ART: Patients are eligible for enrolment after  $\geq 1$  year of virologically suppressive first-line ART and only if a last VL with a result of  $<1000$  copies/mL was performed within the last 6 months. Randomisation is performed 6 months after the last VL result.

A total number of 600 patients will be randomized into two trial arms. The trial will be conducted on-site at one of the clinical facilities of Ndlovu Care Group (<http://www.ndlovucaregroup.co.za/>), one of the partners in the project. This facility, Ndlovu Medical Centre, is situated in the town of Elandsdoorn, Limpopo, South Africa, and provides medical service to local South African patients who are unable to pay medical insurance. The

---

\* In this protocol timing of study visits and procedures is indicated in months (defined as a period of 28 days) after the date on which ART was initiated. For the purpose of this protocol, whenever an event is timed at a certain month, a margin of 28 days before and 28 days after the exact date must be maintained. Hence, if a patient has been on ART since September 4th, 2014, his/her month 6 study follow-up visit is due Thursday, February 19th 2015, and will fall within the time frame of Thursday, January 22nd 2015 and Thursday, March 19th 2015.

Ndlovu Care Group distributes antiretroviral medication in the framework of the South African Department of Health HAART programme. This clinic is currently providing ART to >3600 patients. Patients on ART return to the clinic monthly for collection of medication, pill count and adherence counselling, which allows intensification of monitoring without substantial change of the infrastructure or frequency of visits.

#### 4.3 Inclusion criteria (study baseline)

- HIV-1 infected male or female patients
- For ART Naïve patients: Eligible for first-line ART and intending to initiate first-line ART at the clinical site
- For patients on ART: On first-line ART  $\geq 1$  year. Last VL <6 months ago and <1000 copies/mL
- $\geq 18$  years of age
- Able to understand and willing to give informed consent

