## **Inclusion, exclusion and randomisation criteria**

### **Inclusion criteria**

- HIV-1 infected male or female patients
- For ART Naïve patients: Eligible for and intending to initiate ART at the clinical site
- For patients on ART: On ART  $\geq 1$  year. Last VL <6 months ago and <1000 copies/mL
- $\geq 18$  years of age
- Able to understand and willing to give informed consent

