#### 4.5 Randomisation criteria (month 6)

- Completion of six months of continuous first-line ART.
- For ART Naïve patients: A VL of <1000 copies/mL at the first VL measurement after initiation at month 6 of ART or a VL of >1000 copies/mL at month 6 of ART followed by a VL of <1000 copies/mL before or at month 9 of ART.
- Absence of severe active opportunistic infection requiring therapy at time point of randomisation, excluding infection with *M. tuberculosis*.

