### 5.1.3 Intervention arm follow-up – Intensified HIV treatment monitoring

300 patients randomly assigned to this arm will be monitored using the investigational intensified monitoring strategy. This strategy consists of 3-monthly VL monitoring at month 9, 12, 15, 18, 21 and 24 (after start of ART in initiating patients or after the last VL measurement in patients on ART). If a VL measurement > 1000 copies/mL is detected, the patient will be called back for a follow-up study visit at the next monthly medication collection visit (4 weeks after detection of elevated VL). Upon arrival DLM is performed, the VL measurement is repeated, and a DBS prepared and stored at room temperature. Procedures following this depend on the result of DLM:

- If drug levels are detected by DLM, the result of the VL measurement is awaited. If the repeat VL is >1000 copies/ml, the DBS is shipped directly by courier to the WHO reference laboratory for drug resistance testing. The reference laboratory will provide feedback by means of a digital resistance report to the coordinating research physician. The patient will be called back for a second follow-up study visit at the next monthly medication visit (8 weeks after detection of elevated VL), either for prescription of second-line therapy or continuation of first-line therapy, guided by the

result of resistance testing.

- If DLM at the first follow-up visit indicates that drug levels are not detected, intensified counselling is performed at the same visit and first-line therapy will be maintained, regardless of the result of the repeat VL measurement. The patient will not be called back and the next VL will be performed at the next scheduled three-monthly time point. However, if the VL result at this visit is again >1000 copies/ml, drug resistance testing will be performed regardless of the outcome of DLM.

For a full overview of study visits and clinical algorithms in the control arm, see Figure 1: ITREMA study flowchart.

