#### 5.2.5 Drug Level Monitoring (DLM)

DLM will be performed in case of a VL >1000 copies/ml at any of the intervention arm study follow-up visits. DLM will take place at a call back visit one month after the visit in which elevated VL was detected, using EDTA-derived plasma obtained at the call back visit. DLM will be performed on-site using a qualitative assay that can be implemented in basic clinical laboratories, and will detect plasma levels of the NNRTI's efavirenz and nevirapine. Results will be reported as either “detectable drug level” or “no detectable drug level”, the latter indicating at least several days of non-adherence over the last week. This result will be reported back to the treating research clinician at the call back visit, who will inform the patient of the result during this visit.

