#### 5.2.6 Dried Blood Spot-based Drug Resistance Testing

In case of a confirmed detectable viral load (>1000 copies/ml) in the presence of detectable drug level as indicated by DLM, a dried blood spot (DBS) sample acquired during the second viral load measurement will be sent to a WHO reference laboratory for drug resistance testing, where genotypic HIV-1 drug resistance testing will be performed using an RT-only assay optimized for non-B HIV subtypes. This assay has been validated for use on DBS and implemented in a pilot study at Ndlovu Medical Centre. The assay consists of a single-round one-tube RT-PCR to amplify the viral RT-gene between codons 40-238, followed by population sequencing of the amplified fragment in both directions using 2 primers only. With this approach all RT resistance information relevant to first-line regimens is generated at minimal cost for laboratory reagents, equipment and personnel. If resistance testing is indicated in patients using second line therapy, a protease-only genotypic assay will be performed on the DBS in addition to the RT-only assay. Drug resistance testing will also be performed retrospectively on stored DBS in all patients with therapy failure in the control group, using the same approach as described above. The WHO reference laboratory will provide the treating physician with the result and interpretation of the drug resistance test, containing viral subtype, a list of all mutations, specific indication of relevance of these mutations to drug-resistance, a drug susceptibility ranking using resistance interpretation algorithms, and an overall interpretation with treatment advice taking local availability of antiretroviral drugs into account.

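### Eligibility admits any first-line ART, but the intervention arm's drug level branch sees only efavirenz and nevirapine, so an eligible viraemic patient on neither is classed as non-adherent and genotyped later

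*Protocol*

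**What the plan says.** **Eligibility.** Protocol 4.3 takes treated patients under "For patients on ART: On first-line ART" (at least one year) and untreated patients under "Eligible for first-line ART and intending to initiate first-line ART at the clinical site". Section 4.5 requires "Completion of six months of continuous first-line ART". Section 4.2 also speaks only of first-line ART. None of these names an NNRTI, efavirenz or nevirapine. The Summary is wider: its inclusion criterion reads "For patients on ART: On ART", and its randomisation criterion on six months of treatment likewise lacks the first-line condition.

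**Regimen.** Section 2.1 describes practice without setting a rule: "First-line ART regimens are provided on programmatic basis and usually consist of" two NRTIs with efavirenz.

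**Assay.** Section 5.2.5 says the on-site test "will detect plasma levels of the NNRTI's efavirenz and nevirapine". It reports detectable or not detectable, and takes the second result to mean several days or more without medication in the past week. It makes no exception for a patient prescribed neither drug.

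**Consequence.** After a negative result at the call-back, 5.1.3 says that "intensified counselling is performed at the same visit and first-line therapy will be maintained, regardless of the result of the repeat VL measurement". Section 5.2.4.1 adds that the dried blood spot is not sent and the patient is not called back or switched before the next study visit. Both sections then give a fallback: if viral load is again above 1000 at that visit (day 84), resistance testing is done whatever the drug level result was.

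**The concern.** The drug level result decides which viraemic intervention patients are genotyped promptly. For a patient on efavirenz or nevirapine it carries information about adherence. For a patient prescribed neither, it is negative whatever the adherence, yet the stated rule treats it in the same way. Such a patient would be told that no drug was found, given intensified counselling, kept on the regimen, and not genotyped at that step.

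Early detection of resistance is a stated purpose of the intervention (Summary, Rationale; section 2.2). The number of resistance mutations and the time on a failing regimen are outcomes in 6.1. The misclassification would arise by construction, and only in the intervention arm, because the control arm has no drug level step.

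**Working it through.** The protocol states no figure on this point, so there is none to reproduce. The check has three parts.

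**1. Following an eligible patient on neither drug through the intervention arm**

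- Eligibility (4.2, 4.3, 4.5): met on first-line ART, with no condition on the drugs in the regimen.
- Viral load above 1000 at a study visit (day 0): call-back at day 28 for repeat viral load, drug level test and dried blood spot.
- Drug level (5.2.5): can only be negative.
- Routing (5.1.3, 5.2.4.1): the negative branch applies even if the repeat viral load is above 1000. Pill counts appear in 5.3.1.4 only as a further reason to intensify counselling; nothing there lets a good pill count override a negative drug level.
- Next study visit (day 84): genotyping if viral load is again above 1000.

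The fallback is not stated everywhere. Section 5.3.1.5 says that resistance testing is not done after a negative drug level and does not mention it. In Table 4 the resistance test is marked in the column for two elevated viral loads with a detected drug level, and not in the DL- column.

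**2. Delay to genotyping, from the day counts in 5.2.4.1**

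| Step | Drug level detected | Drug level not detected |
|---|---|---|
| Sample that is genotyped | day 28 | day 84 |
| Dispatch | day 31–33, after the second viral load result | day 84 at the earliest |
| Decision visit | day 56 | after day 84 |

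- Dispatch: 84 − 33 = 51 and 84 − 31 = 53, so at least 51 to 53 days later.
- Sample collection: 84 − 28 = 56 days later.
- Against the usual decision visit: 84 − 56 = 28 days, before any time for the genotype itself.

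**3. Number of patients**

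Inputs: 300 intervention patients (5.1.3) and 20% cumulative virological failure at 18 months (6.7.3). The share *f* of patients on neither drug is not in the protocol, so it is assumed over a range.

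Affected patients = 300 × *f*. Affected failures = 300 × *f* × 0.20, out of 300 × 0.20 = 60, before loss to follow-up.

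| Assumed *f* | Patients | Failures (of about 60) |
|---|---|---|
| 1% | 3 | 0.6 |
| 2% | 6 | 1.2 |
| 5% | 15 | 3 |
| 10% | 30 | 6 |

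The failure counts are upper figures for a given *f*. Only a patient whose repeat viral load is also above 1000 would have been genotyped from the call-back sample, and 6.7.3 does not say that its 20% refers to confirmed failure.

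**The case against.** The strongest reply is that the affected group may be empty. The only first-line regimen that 2.1 describes contains efavirenz, protease inhibitors appear only as second-line treatment, and the flowchart legend speaks of the NNRTI as if every patient had one. The assay also covers nevirapine, so a patient moved from efavirenz to nevirapine is not misread. The screening in 5.2.3 for contra-indications to components of first-line ART does not show that anyone starts without an NNRTI, since the component could be an NRTI. Whether the national programme offers another first-line regimen depends on a guideline that is not part of the document. This stands as far as frequency goes. It does not supply the missing criterion, because a description of usual practice does not limit who may enter.

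A reader might also infer more than the text supports:

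- **That these patients are never genotyped.** Sections 5.1.3 and 5.2.4.1 defer the test to day 84 if viraemia persists; they do not rule it out.
- **That the whole strategy fails for them.** Three-monthly viral load and the fallback genotype still operate. Only the drug level branch fails.
- **That the arm comparison is biased.** This is not shown. Failure due to non-adherence is not an outcome in 6.1. Failure without resistance and averted switches are defined there by viral load and genotype, without the drug level. Section 5.1.3 also plans retrospective resistance testing on stored dried blood spots in therapy failure. At most, time on a failing regimen or mutation accumulation would shift in a few patients.
- **That second-line patients will be randomised and miss protease testing.** The Summary wording would let them in, but 4.2, 4.3 and 4.5 exclude them. For patients on second-line therapy, 5.2.6 provides for a protease assay: "If resistance testing is indicated in patients using second line therapy, a protease-only genotypic assay will be performed on the DBS".

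**Conclusion.** The point holds in this limited form. Eligibility is not tied to the two drugs that the assay can detect, and the Summary is wider than the body of the protocol. Any eligible viraemic intervention patient prescribed neither drug is classed as non-adherent at the call-back, whatever the adherence. Dispatch for genotyping then falls at least 51 to 53 days later than by the usual route and depends on viral load being above 1000 again at day 84.

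The delay follows from the protocol's own day counts. The number affected does not: it rests on the assumed 1 to 10%, which gives at most about 0.6 to 6 of 60 failures, and the true share may be close to zero. The effect on the arm comparison may therefore be small. The case for a change rests on the misclassification of individual patients in one arm, and on passages that do not agree about when a resistance test follows a negative drug level.

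**What to change.** 1. Align the Summary inclusion and randomisation criteria with 4.3 and 4.5 by restoring the first-line condition.
2. Add to 4.3 and 4.5 that the current regimen contains an NNRTI that the drug level assay detects (efavirenz or nevirapine), checked from the clinic record at enrolment and again at randomisation.
3. Reconcile 5.2.5 with 5.1.3, 5.2.4.1, 5.3.1.5 and Table 4 for a patient prescribed neither drug at the call-back. This is needed even with the eligibility change, because a regimen can change after randomisation. The reconciliation should cover the day-84 fallback, which 5.3.1.5 and the DL- column of Table 4 omit. How such a patient is managed is for the sponsor and investigators to settle; the point here is only that the passages must agree.

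The cost is protocol wording and a check of the prescribed regimen at two time points. The downside is that a small number of otherwise eligible patients would not be enrolled.
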